# unless patient has contraindication for CMR

\*\*\* if present

### 3. Introduction

Arrhythmogenic Cardiomyopathy (ACM) is a rare genetic disease characterized by ventricular arrhythmias, increased sudden death risk, and progressive myocardial fibro-adipose replacement leading to heart failure [5]. It is identified by the following OMIM numbers: #609040, #607450, #610193, #610476, #611528, #107970, #604400, #615616, #618920, #602086, #602087, #604401 and forms with unknown genetic origin.

ACM affects ~90,000 people in Europe (prevalence of 1:5000 [6]), mainly young and athletes [7], with a dramatic impact on health and quality of life. Up to 25% of sudden deaths in age <30 years are caused by ACM [8-10]. The affected patients are at risk of cardiac sudden death and heart failure. Thus, they are subjected to a long-life follow-up to monitor symptom worsening and disease progression for cardiac morphological and/or functional impairments, and to optimize the treatment [11].

Current medications include beta blockers, antiarrhythmics, and heart failure drugs [12]. Implantable cardioverter defibrillator is life-saving, despite the morbidity linked to complications and inappropriate shocks. Other invasive procedures are available, such as ablation and end-stage heart transplantation. However, none of these approaches effectively address the underlying pathology. In particular, no specific therapies to prevent the fibro-adipose substitution are available.

#### 3.1. Study Rationale

The present SEARCH TRIAL relies on solid preliminary *in vitro* and *in vivo* data suggesting novel pharmacologically targetable ACM pathogenic mechanisms. Retrospective studies in ACM patients of Centro Cardiologico Monzino IRCCS showed that oxidized low density lipoproteins (oxLDL) plasma levels were associated with severe ACM phenotypes, as increased cardiac lipid accumulation, cardiac dysfunction, and arrhythmic burden. Preclinical studies in an ACM mouse showed that Atorvastatin treatment reduced oxLDL levels and prevented ACM phenotype development [1]. Based on findings of the Centro Cardiologico Monzino IRCCS, we propose that the use of statins in patients suffering from ACM may have beneficial effects in reducing the progression of the pathology and avoiding the most severe consequences of the disease. Indeed, beyond the described canonical lipid-lowering effects, atorvastatin has known pleiotropic effects, as anti-oxidant, anti-inflammatory and anti-arrhythmic, leading, in ACM patients, to lowering of the triggering factor oxLDL, reduction of the inflammatory mediated disease bursts, and moderation of the arrhythmia burden.

#### 3.2. Background

CCM *in vitro* and *in vivo* data laid the basis to propose a novel pharmacological treatment for ACM patients [9]. Briefly, to explain incomplete penetrance and phenotypic variability of ACM, we have shown that an increase in circulating oxidized low-density lipoproteins (oxLDL) is associated with more severe phenotypes (increased cardiac lipid accumulation, RV dysfunction and arrhythmic burden).

We confirmed our hypothesis in disease-relevant models (primary cardiac mesenchymal stromal cells and patient specific induced pluripotent stem cell-derived cardiomyocytes; heterozygous knock-out mouse model for plakophilin 2 (*PKP2*) identifying the molecular mechanism involved [1].

Preclinical studies in the mouse model showed that treatment with atorvastatin, reducing levels of oxLDL, prevents the severe manifestation of the mouse model disease phenotypes (increased cardiac lipid accumulation, cardiac dysfunction, electrocardiographic manifestations) [1].

### 3.3. Benefit/Risk Assessment

If the hypothesis proves to be correct, we expect to slowing down disease progression, both from the tissue and the electrical points of view, and consequently an improvement in symptoms and a reduction in arrhythmic risk.

The proposed therapy is expected to bring significant clinical benefit compared to existing therapies in Arrhythmogenic Cardiomyopathy context, none of which targets the fibro-adipogenic disease progression. The use of statins in patients suffering from ACM may have beneficial effects in reducing the progression of the pathology and avoiding the most severe consequences of the disease. Indeed, beyond the described canonical lipid-lowering effects, atorvastatin has known pleiotropic effects, as anti-oxidant, anti-inflammatory and anti-arrhythmic, leading, in ACM patients, to lowering of the triggering factor oxLDL, reduction of the inflammatory mediated disease bursts, and moderation of the arrhythmia burden.

The expected results will be beneficial for the health system, reducing costs and efforts for the management of ACM patients.

In addition, the patient in the study will be guaranteed close follow-up and more in-depth care than during routine visits.

However, it is possible that a subgroup of patients taking Atorvastatin may experience side effects.

In the database of placebo-controlled atorvastatin clinical trials involving 16,066 patients (8755 Atorvastatin vs. 7311 placebo) treated for an average period of 53 weeks, 5.2 per cent of patients on atorvastatin discontinued the trial due to adverse reactions, compared to 4.0 per cent of placebo-treated patients.

Below is the profile of atorvastatin adverse reactions based on data from clinical studies and extensive post-marketing experience. The frequencies of the estimated reactions are classified according to the following convention: common ( $\geq 1/100$ ,  $< 1/10$ ); uncommon ( $\geq 1/1,000$ ,  $< 1/100$ ); rare ( $\geq 1/10,000$ ,  $< 1/1,000$ ); very rare ( $< 1/10,000$ ); frequency unknown (cannot be defined based on available data).

Infections and infestations

Common: nasopharyngitis.

Haemolymphopoietic system disorders

Rare: thrombocytopenia

Immune system disorders

Common: allergic reactions

Very rare: anaphylaxis

Metabolism and nutrition disorders

Common: hyperglycaemia

Uncommon: hypoglycaemia, weight gain, anorexia

Psychiatric disorders

Uncommon: nightmares, insomnia

Nervous system disorders

Common: headache

Uncommon: dizziness, paresthesia, hypoesthesia, dysgeusia, amnesia

Rare: peripheral neuropathy

Frequency not known: myasthenia gravis

Eye disorders

Uncommon: blurred vision

Rare: visual disturbance

Frequency not known: ocular myasthenia

Ear and labyrinth disorders

Uncommon: tinnitus

Very rare: hearing loss  
Respiratory, thoracic and mediastinal disorders  
Common: pharyngolaryngeal pain, epistaxis  
Gastrointestinal disorders  
Common: constipation, flatulence, dyspepsia, nausea, diarrhoea  
Uncommon: vomiting, upper and lower abdominal pain, belching, pancreatitis  
Hepatobiliary disorders  
Uncommon: hepatitis  
Rare: cholestasis  
Very rare: liver failure  
Skin and subcutaneous tissue disorders  
Uncommon: urticaria, rash, itching, alopecia  
Rare: angioneurotic oedema, bullous dermatitis, including erythema multiforme, Stevens-Johnson syndrome and toxic epidermal necrolysis  
Musculoskeletal system and connective tissue disorders  
Common: myalgia, arthralgia, pain in extremities, muscle spasms, joint swelling, back pain  
Uncommon: neck pain, muscle fatigue  
Rare: myopathy, myositis, rhabdomyolysis, muscle rupture, tendinopathy, sometimes complicated by rupture  
Very rare: Lupus-like syndrome  
More detailed information about the known and expected benefits and risks and reasonably expected adverse events of Atorvastatin may be found in the Summary of Product Characteristic (SmPC).

Overall, the anticipated benefits to the subjects and to public health justify the foreseeable risks and inconveniences and compliance with this condition is constantly monitored

## 4. Objectives and Endpoints

| Objectives                                                                                                                                                                   | Endpoints                                                                                                                                                                                                                                                                                                                            | Measure of the outcome                                                                                                                                                                                                                                                                                                                                                                                                                                                                                                                                                                                                                                                                                                                                                                                                                                                                                                                                                                                                                                                                                                                        |
|------------------------------------------------------------------------------------------------------------------------------------------------------------------------------|--------------------------------------------------------------------------------------------------------------------------------------------------------------------------------------------------------------------------------------------------------------------------------------------------------------------------------------|-----------------------------------------------------------------------------------------------------------------------------------------------------------------------------------------------------------------------------------------------------------------------------------------------------------------------------------------------------------------------------------------------------------------------------------------------------------------------------------------------------------------------------------------------------------------------------------------------------------------------------------------------------------------------------------------------------------------------------------------------------------------------------------------------------------------------------------------------------------------------------------------------------------------------------------------------------------------------------------------------------------------------------------------------------------------------------------------------------------------------------------------------|
| Primary
Efficacy of Atorvastatin in avoiding functional RV deterioration                                                                                           | Deterioration from baseline of RV free wall longitudinal strain measured by ECHO.                                                                                                                                                                                                                                                    | Variation of strain RV free wall longitudinal strain measured by ECHO at T18 respect to T0 (%)                                                                                                                                                                                                                                                                                                                                                                                                                                                                                                                                                                                                                                                                                                                                                                                                                                                                                                                                                                                                                                                |
| Secondary
a) Efficacy of Atorvastatin in avoiding electric, morphological and biomarkers deterioration;

b) safety of Atorvastatin treatment   | a) Deterioration from baseline of
i) arrhythmia burden (PVC, non-sustained and sustained VA, VF, appropriate ICD shocks); ii) other morphological parameters (ventricular volumes, function, both at ECHO and CMR); iii) ECG parameters; iv) blood parameters;

b) monitoring of AE and patient's well-being. | a)
i) Deterioration from baseline of the frequency of premature ventricular contractions, non-sustained and sustained ventricular arrhythmias, episodes of ventricular fibrillation, appropriate defibrillator shocks (measured by Holter, defibrillator and loop recorder interrogation at T18).
ii) Variation from baseline of morphological parameters, such as ventricular volumes (ml), parietal thicknesses (mm), fibrotic replacement characteristics (mm  ), cardiac functional parameters as ejection fraction (%) or Fractional shortening (%), heart movements (number and extension of bulging and wall motion abnormalities) measured at ECHO and CMR at T18.
iii) Variation from baseline of the electrocardiogram parameters (ms or voltage) at T18.
iv) Variation from baseline of biomarkers at T18 (concentrations, Units).
b)
i) Number and severity of adverse events (blood safety parameters variation and number and severity of patient-reported adverse effects) till T18.
ii) Variation in the score of the psychological questionnaires at T18 respect to baseline. |
| Tertiary/Exploratory
a) Validation of prediction models of ACM progression;

b) prediction of differential response to Atorvastatin treatment. | a) Testing the prediction models on the prospectively collected clinical, biological, genetic, and radiomics data of the placebo cohort;

b) testing the association of prospectively collected clinical, biological, genetic, and radiomics data of the Atorvastatin cohort with outcome.                       | a) Verification in terms of sensitivity, specificity, overall predictive performance of the correspondence between the predicted outcome (by different prediction models) and the actual variation at T18 of the clinical, biological, genetic, and radiomics variables of the placebo cohort;

b) association coefficients of the baseline clinical, biological, genetic, and radiomics variable of the Atorvastatin cohort with endpoints outcomes.                                                                                                                                                                                                                                                                                                                                                                                                                                                                                                                                                                                                                                                                     |

## 5. Study Design

### 5.1. Overall Design

This is a multicenter, prospective, randomized, double-blind, placebo-controlled Phase II clinical trial.

The duration of the study for a participant will include:

- patients' enrolment: patients will be enrolled, after written informed consent obtainment, if they meet inclusion criteria and no exclusion criteria are verified.
- randomization: once successfully screened, enrolled participants will receive IMP (either Atorvastatin or placebo)
- treatment period: the patient will take the IMP daily for 18 months. At the beginning (T0 visit) data collection will be performed. During this period the patient will be seen at the second and fourth month for a safety check (T2 and T4 visit), to control for hidden adverse reactions, at month 9 (T9 visit) and at month 18 (T18 visit) for data collection and safety check. Meanwhile, 2 telephone call, at T12 and T15 will be performed to collect patient reported status. In addition, unscheduled visits, for safety reasons are welcome.
- follow-up period: a safety follow-up telephonic check will be performed approximately 1 months after the last dose of IMP (T19).

[figure not shown]

## 5.2. Participant and Study Completion

Approximately 110 participants will be screened to achieve 102 randomly assigned to study treatment and 88 evaluable participants for an estimated total of 44 evaluable participants per treatment group.

## 5.3. Study Time table

Planned starting date (first-patient-in): October, 2024

Projected completion of patient accrual (last-patient-in): March 2025

Projected study end date (last-patient-last-visit): August 2026

Each patient participation is expected to be 19 months from T0 screening visit to T19 follow-up telephone call. This period includes 18 months of treatment and 1 month follow-up.

## 5.4. End of Study Definition

A participant is considered to have completed the study if he/she has completed all phases of the study including the last visit at T18 and having received the telephone call at T19.

The end of the study is defined as the date of the last telephone call at T19 of the last participant in the study.

## 5.5. Rationale for Study Design

Study design. We decided to propose a phase II randomized trial since Atorvastatin is a known, safe and broadly used drug. The safety studies on healthy controls (phase I trials) have been already performed. We will use atorvastatin in a posology as per technical data sheet.

The use of placebo is proposed in order to control confounding factors (e.g. patient and physician suggestions, spontaneous fluctuation of the disease and its symptoms) that may affect the reading of the research results. In particular, the use of the placebo could help in the actual estimation of the side effects of Atorvastatin and the perception of the symptoms of the disease, and of patients's well-being, thus being useful in the secondary endpoint.

Choice of the IMP. Atorvastatin was chosen among statins as has been tested both *in vitro* and *in vivo*. Among the statins it is one of those with a high antioxidant effect [13]. The choice of the brand (Atorvastatina TEVA) is due to the fact that the tablet is relatively simple and smooth, with no color and no writing, therefore easy to reproduce as a placebo tablet. In addition, it is available and easily accessible on the market in Italy.

Choice of primary endpoint. Only few interventional clinical studies for therapy validation have been performed or are ongoing on ACM patients. Some are Phase1, therefore the primary endpoint is safety and tolerability (NCT06109181, NCT06228924, NCT05885412). The ones that test efficacy of therapeutics are the following:

- NCT03685149: "Pilot Randomized Trial With Flecainide in ARVC Patients" to test the efficacy of Flecainide in the reduction of number of ventricular ectopic beats.
- NCT03593317: "Blockade of the Renin-angiotensin-aldosterone System in Patients With ARVD (BRAVE)" to test the efficacy of spironolactone on ventricular myocardial function and remodeling (measured by right ventricle longitudinal strain and right ventricle infundibulum diameter at ECHO) and arrhythmia burden (number of ventricular extrasystoles).
- NCT06174220. Targeted Therapy With Glycogen Synthase Kinase-3 Inhibition for Arrhythmogenic Cardiomyopathy to test ventricular function (change in ventricular strain at ECHO) and PVC burden.
- NCT06275893: IC14 "(Atibuclimab) in Arrhythmogenic Cardiomyopathy" to determine whether IC14 treatment reduces markers of inflammation and disease biomarkers in ACM patients treated with IC14.

-NCT05524077: “Catheter Ablation Versus Anti-arrhythmic Drugs for Ventricular Tachycardia (CAAD-VT)” to test a composite endpoint of Recurrent VT or VT storm or death following the different treatments.

Common primary endpoints are RV function or arrhythmia burden. Those trials assessing RV function use RV strain as outcome.

Accordingly, we chose the primary endpoint outcome to be a clinically relevant measurable parameter. We chose RV longitudinal strains for the following reasons:

- CCM *in vitro* results point to an action of atorvastatin in counteracting the adipogenic differentiation of cardiac cells leading to a moderation of morphological/functional remodeling of the cardiac substrate (of which strain is a measure [14]).
- CCM *in vivo* results showed a significant involvement of the right ventricle respect to the left ventricle.
- RV free wall longitudinal strain reflects the deformation of the RV in the longitudinal direction. In comparison with RV ejection fraction, it is earlier in the detection of systolic disfunction; moreover, it is linked to prognosis in many clinical conditions.
- Free wall longitudinal strain of the RV worsens over the years in ACM patients with little variability, as proven by the CCM cohort retrospective data (n=20 patients with double ECHO): 12.8% (2.4 points of strain) reduction in 18 months with a standard deviation of 4.5%.
- A similar difference of RV strain has recently been confirmed by other group publications [15],[16]. In addition, a similar standard deviation was measured in other cohorts [14].

ECHO parameters are measurable in every patient, while CMR is feasible only if the patient is not carrying an ICD or if the ICD is compatible with CMR. In the last case it suffers of some artifacts.

Secondary endpoints. Secondary endpoints will include other information regarding disease progression. Importantly, arrhythmia burden will be monitored, and it is expected to decrease, as reported for other non-ischemic populations in treatment with statins [17]. Most known clinical markers and biomarkers will be assessed, as well as the novel biomarker oxLDL [1]. In addition, it is important to evaluate safety of Atorvastatin 80 mg administration for the novel indication (ACM patients).

Exclusion criteria. They have been chosen to limit as much as possible the side effects caused by the treatment.

Length of the treatment. The choice of the 18-months treatment is due to the fact that ACM is a progressive disease but in the majority of patients, slowly progressive. A retrospective analysis of our cohort showed a quantifiable mean progression, as RV free wall longitudinal strain in 18 months. Therefore, this is the minimum term in which we could detect a favorable effect of Atorvastatin treatment.

Power analysis. We calculated the trial sample size basing on the clinical data of CCM patient cohort, with double Echo, because little data on disease progression, above all functional cardiac data, are available in the literature. However, a similar sample size has been estimated, based on RV strain, in other, currently recruiting, pharmacological trials in ACM patients (NCT03593317 and NCT06174220), who recruit 120 patients and measure the outcome at 1 year or 6 months respectively.

In calculating the sample size, we had to keep into account that ACM is a rare disease, therefore we had to discard all the endpoints that we tested which gave as result an unreachable sample size. A reachable criterion would have been the quantity of PVC in the 24 hours. However, we believe that the effect of atorvastatin is only indirectly likely to affect arrhythmic burden (since it was demonstrated to impact the RV function, primarily). Besides, it is very variable and it would have needed a larger cohort.

In addition, we have been conservative in considering 15% possible drop-out, since we are aware that it is more likely that an adverse event or patient withdrawal happens in the context of a long treatment.

Patient recruitment. Patients will be recruited throughout different centres in Italy. The involvement of several centres is essential to guarantee the recruitment of many patients in the context of a disease with a prevalence of 1:5000, of which the majority are male patients [18] and athletes are frequent [19]. The inhomogeneity of the different cohorts will, from one part, account for a higher variability of the results, from the other will guarantee real world data, and applicability of the results of the trial to a broader ACM population.

Safety and compliance. Patients will be monitored approximately every 3 months either by an outpatient visit or through a telephone call, to screen adverse events, serious adverse events and suspected unexpected adverse events, and to check on therapy compliance. For safety needs, patients can be subjected to unscheduled visits.

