|                                     |          |    | T2 Visit,
Safety check  | T4 Visit,
Safety check | T9 Visit,
data
collection | T12 Phone
call, safety
check | T15 Phone
call, safety
check | T18 Visit,
data
collection |                                                 |
| Psychological questionnaires        |          | X  |                            |                           | X                               |                                    |                                    | X                                |                                                 |
| Blood withdrawal for genetics       |          | X* |                            |                           |                                 |                                    |                                    |                                  |                                                 |
| Blood withdrawal for ACM biomarkers |          | X  |                            |                           | X                               |                                    |                                    | X                                |                                                 |
| Patient-reported outcome collection |          |    | X                          | X                         | X                               | X                                  | X                                  | X                                | X                                               |
| Study treatment adherence check     |          |    | X                          | X                         | X                               | X                                  | X                                  | X                                |                                                 |
| AE review                           |          |    | X                          | X                         | X                               | X                                  | X                                  | X                                | X                                               |
| SAE review                          |          |    | X                          | X                         | X                               | X                                  | X                                  | X                                | X                                               |

\* only if not preformed previously

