## **7.5. Preparation/Handling/Storage/Accountability**

The Investigational Medicinal Product (IMP) consists of Atorvastatin Teva Italia 80 mg film-coated tablets (an approved prescription medicine - class A, based on atorvastatin calcium salt, belonging to the therapeutic group Statin hypolipidemizers) as 1 tablet/die or placebo.

Atorvastatin will be purchased from commercial vendors, placebo will be produced, in accordance with the principles and guidelines of Good Manufacturing Practice (GMP) for Medicinal Products, in an authorized pharmaceutical manufacturer. Batch release certificate will be provided together with the IMPs.

Packaging and labelling of both Atorvastatin and Placebo will be performed by Euromed Pharma Services S.r.l. in accordance with the Regulation (EU) No 536/2014 (see Annex II) In particular, kits will be prepared in boxes, containing 12 blisters of 10 tablets each and labelled with the randomization codes. Each participating centre will be supplied with an adequate number of IMP. The IMP will be securely stored at room temperature.

This trial will use the Redcap CRF as electronic drug accountability system and pharmacy records (attached as Annex III). All shipping and receiving invoices indicating the type and quantity of the IMP and the date of shipment will be recorded at each site. Responsible investigators at each centre are required to maintain adequate records of the disposition of the IMP.

After the randomization, the Investigators will record into the CRF the kit number assigned to the patient and will dispense an adequate number of kits to comply with the study treatment until the following visit.

Before receiving the first kit of study treatment, patients will be instructed in using, handling, storing, and returning of IMP.

At each study visit the patient will return the empty batches to the site and those close to the expiry dates. The investigators will check the reconciliation between dispensed and returned IMP and will dispense it again. The accountability will be documented into the CRF and in the pharmacy record form at each study visit.

In addition, to monitor the patient's compliance to IMP about every 3 months will be performed a telephone call-visit. The treatment will last 18 months for each patient.

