#### **7.5.4. Treatment Compliance**

Adherence will be checked during each visit and the patient's compliance to IMP about every 3 months will be performed a telephone call/visit.

IMP tablet count is the method to assess compliance to therapy.

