#### **T4 Visit Safety check (4nd month +/- 1 month)**

This visit includes:

- Full physical examination
- Pregnancy test (WOCBP only)
- Blood withdrawal for hepatic and muscle functionality
- Patient-reported outcome collection
- Study treatment adherence check
- AE review
- SAE review

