#### **T9 Visit Data collection (9th month +/- 1 month)**

This visit includes:

- IMP supply (3 kits)
- Full physical examination
- Pregnancy test (WOCBP only)
- Blood withdrawal for hepatic and muscle functionality
- 12-lead ECG
- ECHO
- Holter ECG
- ICD/ILR interrogation
- Psychological questionnaires (i.e. SF-36; HADS; IES-R)
- Blood withdrawal for biomarkers
- Patient-reported outcome collection
- Study treatment adherence check
- AE review
- SAE review

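### The protocol promises safety and compliance contact about every 3 months, but schedules none in the 5 months between T4 and T9

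*Protocol*

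**What the plan says.** Three places in the protocol give a contact interval of about 3 months:

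- Section 5.5 (Safety and compliance): "Patients will be monitored approximately every 3 months either by an outpatient visit or through a telephone call". The stated purposes are screening for adverse events, serious adverse events and suspected unexpected events, and checking compliance.
- Section 7.5, for compliance: "to monitor the patient's compliance to IMP about every 3 months will be performed a telephone call-visit". This is introduced as an addition to the kit-return procedure at visits.
- Section 7.5.4, again for compliance: "the patient's compliance to IMP about every 3 months will be performed a telephone call/visit".

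The operative schedule is in section 5.1, the Schedule of Activities (SoA) and section 8.1.4, which agree with one another. After T0 the on-treatment contacts are visits at T2, T4, T9 and T18 and calls at T12 and T15, each with a window of +/- 1 month. Section 5.1 fixes the number of calls: "Meanwhile, 2 telephone call, at T12 and T15 will be performed to collect patient reported status". AE review, SAE review and the adherence check take place at T4 and next at T9. Section 8.5 refers to the SoA for the timing of safety assessments.

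**The concern.** The stated frequency and the schedule cannot both be right for the stretch from T4 to T9. For AE and SAE review, a site that follows section 8.5 to the SoA finds no contact there. For compliance, a site could read section 7.5 as asking for a call in the gap, while a site working from the SoA and section 8.1.4 would not make one.

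What is at stake is limited: later planned safety review and later planned adherence contact in one interval. It still has some weight. Section 5.5 itself treats the safety of 80 mg in this new indication as important to evaluate, and the number and severity of adverse events is a secondary endpoint. The 24-hour SAE clock in section 8.3.3 starts when the investigator learns of the event, and in the gap that depends on the patient coming forward without a planned prompt. Section 8.2.2 allows interruptions of up to 15 consecutive days, so a longer one that began soon after T4 could escape every planned contact for almost 5 months.

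**Working it through.** **Inputs.** Contact times and windows come from the SoA and section 8.1.4; T0 is day 0. The windows in months are T2 1–3, T4 3–5, T9 8–10, T12 11–13, T15 14–16 and T18 17–19.

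**The plan's own figure.** As an average, the 3-month figure reproduces: 18 months / 6 contacts after T0 = 3.0 months. As spacing between contacts it does not.

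**Intervals.** For contacts at months a and b (a < b), the nominal interval is b − a, the shortest allowed is (b − 1) − (a + 1), and the longest allowed is (b + 1) − (a − 1). T0 has no window.

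| Interval | Nominal (months) | Shortest | Longest |
|---|---|---|---|
| T0–T2 | 2 | 1 | 3 |
| T2–T4 | 2 | 0 | 4 |
| **T4–T9** | **5** | **3** | **7** |
| T9–T12 | 3 | 1 | 5 |
| T12–T15 | 3 | 1 | 5 |
| T15–T18 | 3 | 1 | 5 |

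T4–T9 is the only nominal interval above 3 months, and it exceeds the stated spacing by (5 − 3)/3 = 67%. It meets 3 months only if T4 is a full month late (month 5) and T9 a full month early (month 8).

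**Wait to the next planned contact.** Assume an event that the patient does not report and that starts at a uniformly random time between T4 and T9.

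- Current schedule: mean 5/2 = 2.5 months, longest 5 months.
- With a call at month 6 or 7, the gap splits into 2 and 3 months (in either order): mean (2² + 3²)/(2 × 5) = 13/10 = 1.3 months, longest 3 months.
- At the stated 3-month spacing: mean 3/2 = 1.5 months. The shortfall against the protocol's own statement is therefore 2.5 − 1.5 = 1.0 month on average.

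**Windows after adding a call with +/- 1 month.**

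- Call at month 6 (5–7): T4–call 2 (0–4), call–T9 3 (1–5).
- Call at month 7 (6–8): T4–call 3 (1–5), call–T9 2 (0–4).

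No nominal interval then exceeds 3 months. The longest interval the windows allow falls from 7 to 5 months. It does not fall further, because the three intervals after T9 can already reach 5.

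**The case against.** The strongest reply is that the 3-month figure summarises the schedule loosely. It is qualified as approximate, section 5.5 is a rationale rather than a procedure, and six contacts in 18 months do average 3.0 months. The schedule is deliberately front-loaded, with two early safety visits, and the operative sections are consistent with one another. The addition in section 7.5 can be read as additional to kit reconciliation rather than as a separate series of calls. Patients are also encouraged to report adverse events spontaneously (section 8.5), unscheduled visits are allowed (sections 5.1 and 5.5), and T9 has AE and SAE review, safety bloods and an adherence check. On this view, rewording three sentences to point to the SoA would be enough.

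Part of this stands. The mitigations are real and keep the point small. The 24-hour SAE clock starts on awareness in every interval, not only this one. Divergence between sites is a possibility that the wording leaves open; nothing shows that it will happen. The 7-month figure needs both windows at their extremes, and 5 months is the fair headline.

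The average does not rescue the text. A contact every 3 months describes spacing, and the average comes out at 3.0 only because two 2-month intervals offset a 5-month one. Rewording would remove the contradiction, but only by withdrawing the monitoring that the protocol says patients will have.

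**Conclusion.** The concern holds and is minor. The protocol states a monitoring interval that its schedule does not provide between T4 and T9, where the planned gap is 5 months nominal. The interval arithmetic needs no assumption beyond the stated visit times and windows. The mean waits of 2.5 and 1.3 months assume uniform onset within the gap and no spontaneous report, so they describe only events that the patient does not raise and that do not lead to an unscheduled visit. The primary endpoint analysis, the sample size and the missing-data rule in section 9.1.4 are unaffected.

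**What to change.** Add one telephone safety and adherence call at about month 6–7 (+/- 1 month) to section 5.1, the SoA and section 8.1.4. Give it the content of the T12 and T15 calls: patient-reported outcomes, adherence check, AE review and SAE review. Section 7.5.4 says "IMP tablet count is the method to assess compliance to therapy"; adherence at this call would be self-report, as at T12 and T15, and the tablet count would stay at the visits. Sections 5.5, 7.5 and 7.5.4 should then refer to the SoA, so that a single schedule governs.

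The cost is at most 102 × 1 = 102 short calls by existing site staff, plus a written amendment submitted to the ethics committee and the competent authority as appropriate (section 12.3). On the planned timetable in section 5.3, the calls fall between April 2025 (October 2024 + 6 months) and October 2025 (March 2025 + 7 months). Patients already past that point when the amendment takes effect would not receive the call, so 102 is an upper bound.
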